#### RQ5: What long-term change in outcomes is observed at the group level?

Baseline (T0) and follow-up questionnaires (T3 (end of intervention), T4 (3 months after T3), T5 (6 months after T4) will be used to assess long-term change in measured outcomes (i.e. FSE, fatigue, participation, life satisfaction, and perceived health), moderators (i.e. illness identity and mastery) and mediators (i.e. physical activity and sleep) at group level (Fig. 1). We will use linear mixed-effects models with time as a fixed effect and a random intercept for participants to account for the repeated follow-up measurements within individuals. If model assumptions are severely violated, a non-parametric alternative will be considered.

### Interim analyses {21b}

Not applicable.

### Methods for additional analyses (e.g. subgroup analyses) {20b}

Not applicable.

### Methods in analysis to handle protocol non-adherence and any statistical methods to handle missing data {20c}

If missing data exceeds 30–40%, we consider imputation where possible to retain power (Table 1). To guide this decision, we will first examine the missing data mechanism to determine if imputation is valid and, if so, which method is most suitable, such as using multiple imputation methods suitable for time-series data [63].

### Plans to give access to the full protocol, participant level-data and statistical code {31c}

External researchers can apply for access to the data by submitting their research proposal to the principal investigator of this study. Studies concerning youth with chronic illnesses, fatigue, and those involving extensive repeated measurements may be eligible to use the data.

## Oversight and monitoring

### Composition of the coordinating centre and trial steering committee {5d}

The Wilhelmina Children’s Hospital, part of the UMC Utrecht, is the coordinating centre of the present study. The research group, including the principal and executive investigators, will meet weekly to manage the study.

### Composition of the data monitoring committee, its role and reporting structure {21a}

As the study is not subject to the Medical Research Involving Human Subjects Act, no data monitoring committee has been created.

### Adverse event reporting and harms {22}

No study-related adverse events are expected due to this negligible risk. In case of adverse events, these will be documented, and necessary medical follow-up will be provided.

### Frequency and plans for auditing trial conduct {23}

As the study is not subject to the Medical Research Involving Human Subjects Act, no independent monitor is appointed.

### Plans for communicating important protocol amendments to relevant parties (e.g. trial participants, ethical committees) {25}

Modifications will be shared via the website of the eHealth Junior Consortium (ehealthjunior.nl) after consultation of the research quality coordinator of the UMC Utrecht.

### Dissemination plans {31a}

We intend to share the results of the described study with the scientific community via (inter)national conferences and publication(s) in peer-reviewed journal(s). Results will be shared with a wider public via eHealth Junior Consortium partners, including patient organisations, as well as via popular science articles.

## Discussion

Fatigue is a common debilitating symptom in children with a chronic health condition. At an early stage, the personalised transdiagnostic intervention Booster could prevent persistent fatigue and its impairments by increasing FSE. It makes use of innovative methods by combining tailored ESM-insight, mHealth and healthcare professional support. This single-case multiple baseline study examines Booster’s effect on FSE and other outcomes. Understanding of the group level results will be enhanced by extensive explorative analyses at the single-case level. Furthermore, this study enables a deeper understanding of participant characteristics related to change.

A key strength is exploring ESM’s potential as a clinical tool in paediatric health care, as a step towards its implementation. The use of ESM for personalised insight is non-existent in paediatric clinical practice [64, 65]. Neither has ESM as an intervention been studied in children with somatic health conditions [64], except in earlier PROfeel studies [33, 34, 48, 50]. Other studies did show ESM’s value in adolescent [66, 67] and adult mental health care [68–70], and even specifically for fatigue after cancer-treatment [71, 72]. This study aims to pioneer the use of ESM for personalised insight in paediatric health care, building on its established success in adolescent and adult mental health.

Second, building on PROfeel’s feasibility and usefulness for children with chronic health conditions [50], and its effectiveness in youth with persistent fatigue [33, 34], this study addresses three major remaining questions: (1) is ESM for personalised insight effective as early intervention? (2) which intervention elements influence which outcomes for whom, and when? and (3) how do adolescents evaluate the Booster intervention in general and the app specifically?

With regard to (1), the multiple baseline SCED enables showing effectiveness at the group level, while limiting the sample size needed compared to a traditional randomised controlled trial, saving time and resources.

With regard to (2), the intensive longitudinal data collection in the single-case design will clarify the preventative working mechanisms of a paediatric ESM intervention. Although we hypothesise that FSE change coincides with the Insight Conversation, change might already occur during the Measurement Period. Filling out ESM surveys may be an intervention on its own, as self-monitoring can increase emotional awareness and reduce symptoms of depression in young people [66, 67]. Collecting data on multiple outcomes before and during each Booster stage, followed by the change-point analyses (RQ3), will give direction on which intervention elements affect specific outcomes for whom.

With regard to (3), Booster is the result of an extensive iterative and multistakeholder codesign process. The largest changes were made to the smartphone app, in which game mechanics (e.g. rewards and a minigame) were incorporated to sustain motivation throughout the intervention, and the Experiment Module was added. Involving adolescents in the design process ensured a greater understanding of their needs and gave room to incorporate their ideas. This could increase the success of the intervention [73]. A strength of this study is the ongoing input from adolescents. Through the usability questionnaire and qualitative evaluation, their feedback will inform and guide future developments.

A third strength of this study is the embedding in the interdisciplinary eHealth Junior consortium (ehealthjunior.nl) with the involvement of researchers with diverse expertise (e.g. ESM-methodology, psychology, paediatrics, implementation sciences, and game design) and non-academic partners (e.g. patient associations and health care insurers) is secured [74].

However, the study faces several challenges. First, in order to mirror the heterogeneous clinical practice, the inclusion criteria are broadly defined, with a low fatigue severity threshold of ≥ 15 points with the pSFQ. This corresponds to the upper 50th percentile of children with a chronic health condition) [45]. This may result in a diverse group of participants, limiting result replication. Nevertheless, this approach acknowledges the large intra-individual differences in fatigue and thereby strengthens the ecological validity of our results. Also, the additional analyses at the single-case level will shed light on intra-individual differences (RQ2 and 3). Ultimately, our study aims to identify the value of the Booster intervention for adolescents with a chronic health condition who experience hindrance by fatigue.

Second, the study is only powered to demonstrate causal medium to large intervention effects at the group level (RQ1),[37, 52] while one might expect smaller effects. Nevertheless, these smaller intervention effects can be observed with the PDT at the single-case level (RQ2), albeit without causal inference. However, if effects are replicated across individuals and also align with the timing of specific Booster intervention stages, the results of the PDT build a case for treatment efficacy, making alternative causal explanations less likely [39].

Third, we must consider the potential detrimental effect of intensive longitudinal data collection. While most participants in ESM studies reported heightened awareness from repeated measurements as positive, some experienced adverse effects [50, 75–77]. Repeated self-reflection can lead to effective cognitive processing and problem-solving but may also increase internalising symptoms [78]. In our study, intensive longitudinal data collection occurs through ESM surveys during the four-week Measurement Period and the daily progress monitor throughout. It serves both treatment and research purposes. We carefully balanced measurement burden (e.g. minimising items, personalised timing, distraction options in the Booster app, and contact with the investigator, exploring long-term effects with pre-post design instead of extending the daily progress monitor) with validity and scientific rigour (e.g. personalised Booster reports, single-case insights, validated items with strong psychometric properties, and sufficient measurements for statistical power).

A fourth limitation of this study is that to minimise the measurement burden, our primary outcome is measured with a newly developed single-item question, which risks the generalisability of the findings. To minimise this, in the development of the item, we followed the guide by Bandura to construct self-efficacy scales [79], and established face validity with the target population. In the analyses, we will check concurrent validity via correlation with other outcome measures and the baseline and follow-up questionnaires [80]. Afterwards, we will add the item to the ESM-item repository (esmitemrepository.com) for future use by other researchers.

To conclude, we will study the effect of the Booster intervention at the group level while also providing a more detailed understanding at the single-case level by using a multiple baseline SCED. This study builds on earlier studies with PROfeel, Booster’s predecessor. The intervention has evolved in collaboration with patients, clinicians and interdisciplinary stakeholders from the eHealth Junior consortium. Booster aims to avert progression of fatigue and to prevent its impairments in children with chronic health conditions by increasing FSE. It is an example of an in-depth investigation of an early intervention for which small intervention effects are expected. This study will be a stepping stone for the implementation of ESM tools for personal insight in clinical practice.

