### Trial design {8}

This study employs a multiple baseline single-case experimental design (SCED). In a SCED, each case (i.e. each individual) serves as its own control, facilitated by intensive longitudinal data collection in two phases: Phase A (baseline) and Phase B (intervention) [36]. Randomisation of intervention start mitigates potential confounding of time due to external factors (*history*, e.g. transition from winter to summer*)* and internal factors (*maturation*, e.g. spontaneous recovery) [37]. This enhances internal validity [38], as does studying the effect across individuals with a multiple baseline design [38, 39]. Change relative to the randomised intervention start moments allows for causal inference within a SCED. Therefore, in this study, multiple participants start the Booster intervention at a randomised point in time to allow investigation of causal relationships between the intervention and study outcomes at the group level. Data is collected daily for 130 days (nearly nineteen weeks) with ESM via the Booster app on the participants’ phones.

ESM is also known as ecological momentary assessment (EMA). ESM is a validated structured diary method integrated into daily life [40]. It captures personal experiences and behaviours along with real-time fluctuations in well-being through repeated surveys over a period ranging from several days to weeks [41]. In the following sections, the ESM use is detailed, both the daily ESM for measuring study outcomes in the daily progress monitor and the intensive ESM for personalised insight in fatigue. Based on the Internal Validity subscale of the 15-item Risk of Bias in *N*-of-1 Trials (RoBiNT) Scale, our study design has fair methodological rigour (Suppl. Table 1) [38, 42]. Examples of factors strengthening the internal validity are the long intensive longitudinal data collection and the measurement of intervention adherence. SPIRIT reporting guidelines were followed in this protocol [43]. An overview of the study design is given in Fig. 1 (Suppl. Fig. 1 for more details).

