##### Stage 2: Measurement Period

For four weeks, the participant receives the intensive personalised ESM-survey five times daily via the Booster app with an approximate three-hour interval. The first survey of the day arrives at 9 AM, 10 AM, or 11 AM, based on the participant’s schedule choice during the Start Conversation. The exact timing of notification is randomly assigned within 30 min of the scheduled times. In case of non-response, reminders are sent after 20 and 60 min. After 90 min without response, the survey closes and is marked as missing. Completing the intensive ESM-survey costs less than one minute.

From PROfeel research [34], we know that a compliance of at least 35% (i.e. 49 completed surveys) is required to derive a Booster Report. Yet, the reliability of the output increases as the number of completed surveys does. Therefore, in line with previous research [48], we aim for at least 70% compliance. Extension of the Measurement Period will be offered to the participant in case of < 70% compliance. If the participant does not want to extend the Measurement Period, the researcher must discuss the content of the report with more caution because of the lower reliability (see section “Stage 3: Insight Conversation”).

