### Sample size {14}

The power to detect an intervention effect with a multiple baseline design (RQ1) depends on the autocorrelation of consecutive daily progress monitor measurements, the start moment range, the number of repeated measurements, the intervention effect, and the number of cases [52]. In the earlier PROfeel study [48], the median autocorrelation of weekly measurements was 0.17 for FSE, 0.30 for fatigue severity, and 0.09 for QoL. Median autocorrelation of the five times daily ESM item on fatigue severity was 0.37 [48]. We expect the daily measurements in this study to show a higher autocorrelation than weekly measurements, but lower than a five times daily item. Thus, we assumed the autocorrelation in our study to be 0.30 across outcomes. The start moment range is nine, as the Booster intervention is randomised to start (T1) ten to eighteen days after the start of the daily progress monitor (T0). With 100% compliance, the number of repeated measurements is 130. With the abovementioned assumptions and inclusion of twenty cases, with up to 30% of daily measurements missing, the multiple baseline single-case randomisation test (SCRT) can detect medium to large intervention effects of ≥ 0.7 with a power of ≥ 0.80 at the group level (RQ1, Table 1). However, we anticipate small intervention effects since Booster is an early intervention, not treatment. The SCRT, used in SCED, has limited power to detect such small intervention effects [37, 52, 53]. In contrast, the permutation distancing test (PTD), developed for testing differences in means in single-case observational designs (SCODs), exhibits higher statistical power [53]. It is important to note that SCOD cannot establish causality. With the abovementioned assumptions, with up to 40% of daily measurements missing, the study is well powered to observe changes in outcomes for effect sizes as small as 0.3 at the single-case observational level (RQ2, Table 1).

**Table 1 Tab1:** Power for detecting intervention effects at the group and single-case level

Factors influencing power	Study design	
Autocorrelation (%)	30	
Repeated measurements (*n*)	130	
Power (%)	≥ 80	
Cases (*n*)	20 (group level)	1 (single-case)
Test	Multiple baseline SCRT	PDT
Start moment range (*n*)	9	NA
Maximum percentage missing data to retain sufficient power (%)	30	40
Minimum detectable effect size	0.7 (medium to large)	0.3 (small)

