### Data collection and management

#### Plans for assessment and collection of outcomes {18a}

Study outcomes will be assessed using the daily progress monitor, a repeated survey. The Booster app sends the daily progress monitor at a random time within the hour before bedtime. Participants determine the exact timing of completing the monitor, provided it is within three hours of receiving the notification. Responses not submitted within this three-hour window are considered missing. For each item, participants are asked to reflect on their day. Item order is randomised to minimise method bias [56]. The daily monitoring period starts ten to eighteen days before the Start Conversation and continues for 130 days, ending twelve weeks into the Experiment Period.

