## Statistical methods

### Statistical methods for primary and secondary outcomes {20a}

#### RQ1: What is the effect of the Booster intervention on the study outcomes at the group level?

We will study change in mean level of outcomes (level change) after outcome-specific lags (Suppl. Figure 1). We hypothesise that FSE, Booster’s main target, will improve immediately after the Insight Conversation. Improvements in fatigue and participation are expected four weeks later, with life satisfaction and perceived health improving at six weeks post-Insight Conversation. After visual inspection of the data, the multiple baseline SCRT will determine the presence of significant medium to large Booster intervention effects at the group level. The null hypothesis is that observed outcomes are independent of intervention phase. The randomisation of intervention start is a precondition for conducting the SCRT. It tests significance by comparing the observed test statistic (mean level change) to the test statistic distribution of all other possible intervention start points. This controls for time-related confounding [60, 61]. The SCRT outcomes will show if the Booster intervention is effective at the group level.

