#### RQ2: What changes are observed in study outcomes at the single-case level during the Booster intervention?

Second, we will use the permutation distancing test (PDT) and single-case interrupted time series analysis (ITSA) to explore changes at the single-case level during the Booster intervention. The PDT will test the null hypothesis that observations within one individual are evenly distributed between Phase A and B. The PDT compares the observed test statistic (mean level change) to the test statistic distribution of permuted orders of observations. To create this distribution, the PDT uses different subsets of observations with a specific time distance to compensate for serial autocorrelation [53]. With the ITSA, a regression model is fitted to the data, allowing for separate intercepts and slopes in Phase A and B, while correcting for serial autocorrelation [54]. Although neither test can directly establish causality (e.g. the PDT was developed specifically for AB-phase SCODs) [53], together they complement the group-level SCRT results by identifying which individuals show significant change in outcomes in Phase B (responders) and which do not (non-responders). This triangulation approach leverages the strengths of both tests (e.g. the non-parametric PDT has no distributional assumptions, the ITSA enables trend analysis) and provides a comprehensive understanding of the data. In particular, the ITSA helps determine whether significant level changes found could be attributed to trends in the data instead of a possible intervention effect [54]. The combined results from both statistical tests strengthen the overall evidential basis, suggesting increased robustness and reliability of the findings.

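### Replicated, stage-aligned PDT changes do not separate Booster from recovery that runs from enrolment, because the stages differ by only about nine study days between participants

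*Protocol article*

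**What the plan says.** Trial design relies on the randomised start to deal with time-related confounding, and names spontaneous recovery as one such threat: "Randomisation of intervention start mitigates potential confounding of time due to external factors" and internal ones. The stagger is set under Sample size: "The start moment range is nine, as the Booster intervention is randomised to start (T1) ten to eighteen days after the start" of daily monitoring. A fixed interval follows (Stage 2: "For four weeks, the participant receives the intensive personalised ESM-survey five times daily"), and then the Experiment Period; monitoring "continues for 130 days, ending twelve weeks into the Experiment Period".

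Under RQ1, fatigue-related self-efficacy (FSE) "will improve immediately after the Insight Conversation". For the other outcomes, "Improvements in fatigue and participation are expected four weeks later, with life satisfaction and perceived health improving at six weeks" after that conversation.

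Under RQ2, the PDT compares Phase A and Phase B means against permuted orders of one person's observations. The ITSA is run alongside it: "the ITSA helps determine whether significant level changes found could be attributed to trends in the data instead of a possible intervention effect". RQ3 adds change-point analysis for participants who show a change. RQ4 labels FSE responders by the PDT alone.

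The Discussion, in its second challenge, says that smaller effects can be seen with the PDT but not interpreted causally. The next sentence then says that, given replication and alignment with Booster stages, "the results of the PDT build a case for treatment efficacy, making alternative causal explanations less likely".

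**The concern.** The protection against maturation described in Trial design belongs to the randomisation, and so to the SCRT. The PDT does not use the assigned start and makes no allowance for trend.

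Participants are selected for current fatigue, enter after a fatigue work-up and complete a daily diary. Spontaneous recovery, regression to the mean and habituation to the diary would all run from enrolment. Every participant reaches each stage at nearly the same study day, so such a process can produce a Phase A to Phase B difference in several participants. If the process is abrupt, it can produce one close to a stage. Replication then argues against chance, but not against a shared time course.

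The protocol anticipates small effects and concedes that the SCRT has limited power for them. This sentence is therefore the likely route to any efficacy statement. At stake is a reported case for efficacy when participants simply improved with time after enrolment.

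**Working it through.** **1. The plan's own figures.** Start range: 18 − 10 + 1 = 9. Longest schedule: 18 + 28 + 84 = 130 days. Both agree with the article. A simulation of the SCRT (20 cases, autocorrelation 0.30, 30% missing, one-sided 5% assumed) gives power of 0.83, 0.83 and 0.81 for a 0.7 effect starting at T2, four weeks later and six weeks later. The stated 0.80 is reproduced. At 0.3 the power is about 0.27 to 0.32, so the fallback matters.

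**2. Stage windows in study days.**
- T1: 10 to 18 (Sample size).
- T2: 10 + 28 = 38 to 18 + 28 = 46 (Stage 2).
- T2 + 4 weeks: 66 to 74. T2 + 6 weeks: 80 to 88 (RQ1).

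These windows are nominal. Extension of the Measurement Period and weekend shifts of the start can widen them, but neither is randomised.

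**3. What a steady drift does to the phase means.** With Phase B lasting 84 days, the mean day in A is (T2 + 1)/2 and in B is T2 + 42.5. The gap is T2/2 + 42, which is 61 days at T2 = 38, 63 at T2 = 42 and 65 at T2 = 46. A linear recovery of R SD over 130 days gives a difference of R × 63/130 = 0.485R at the centre. That is about 0.24, 0.36 and 0.48 SD for R = 0.5, 0.75 and 1.0. Over all nine starts the multiplier runs only from 61/130 = 0.47 to 65/130 = 0.50, so the start drawn hardly matters.

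**4. How often this looks like a stage-aligned change.** Single-case simulation with autocorrelation 0.30, 30% missing and two-sided 5% (the article states no alpha). An autocorrelation-adjusted mean-difference test stands in for the PDT, and a single CUSUM change point for Wild Binary Segmentation.

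| Truth | Significant A–B difference | Significant and change point within 7 days of T2 |
|---|---|---|
| No effect, linear recovery 0.5 SD | 15% | 6% |
| No effect, linear recovery 0.75 SD | 26% | 7% |
| No effect, linear recovery 1.0 SD | 40% | 12% |
| True step at T2, 0.3 SD | – | 10% |
| True step at T2, 0.5 SD | 42% | 23% |
| No effect, step on common day 42, 0.5 SD | – | 21% |

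In 20 participants the recovery rows give 20 × 0.15 = 3, 20 × 0.26 ≈ 5 and 20 × 0.40 = 8 significant changes. On the joint condition they give 20 × 0.06 ≈ 1 to 20 × 0.12 ≈ 2. With no drift about 5% are significant. An early-levelling recovery (30-day time constant) of 0.5 and 1.0 SD gives about 15% and 37% significant. The rates depend on the stand-in: for a 1.0 SD linear recovery, other versions of the test gave from 30% to 62%.

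**5. Does timing follow the assigned start?** Under a true step of 0.3, 0.7 or 1.0 SD, the correlation between the estimated change point and the assigned T2 is 0.01, 0.07 and 0.15. Nine days of stagger are too few for single-case change points to show whether change tracks Booster or days since enrolment.

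**6. The planned trend check.** The ITSA level term gives 2% to 6% false positives under linear or exponential recovery. Under a logistic recovery centred on day 42 the rate is 11% to 23%, and under a common-day step of 0.7 to 1.0 SD it is 22% to 37%. Its power for a true 0.3 SD step is about 10%.

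**7. The SCRT under the same drift.** Its false-positive rate is 0.06 at 1 SD and 0.05 at 2 SD of linear recovery, near nominal.

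**The case against.** The Discussion asks for replication and stage alignment together, and alignment does discriminate. A reader might infer that natural recovery would meet the condition just as readily as a real effect, so that the argument fails outright. The documents do not support that. A smooth drift has no change point at T2. Under linear recovery a change point falls within 7 days of T2 in 11% to 18% of cases, close to the 15/130 ≈ 12% expected by chance, against 51% and 72% for a true step of 0.7 and 1.0 SD. Where significance is about equal (1.0 SD recovery and a true 0.5 SD step, both near 40%), the joint rate is 12% against 23%.

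The text is also hedged. It disclaims causal inference from the PDT in several places, says only that other explanations become less likely, assigns the ITSA to look for trends, and places causal inference on the SCRT. Recruitment was planned over about six months, which weakens shared calendar events. At least three months of fatigue is required at entry, selection is on the fatigue score and not on FSE, and no document gives a size for natural recovery.

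All of this stands, and it narrows the point without removing it. At 0.3 SD, the size the fallback exists for, a true step meets the joint condition about as often as a 0.5 to 1.0 SD recovery does (10% against 6% to 12%). A step shared in study time is not separated at all. The sentence also reinstates an inference directly after disclaiming it, and the ITSA result does not enter the RQ4 responder label.

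**Conclusion.** The point holds as a limit on interpretation. Replicated, stage-aligned PDT changes make chance and shared calendar events less likely. They do not separate Booster from processes that run from enrolment, which include the spontaneous recovery that the protocol itself names.

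Without any intervention effect, about 3 to 8 of 20 participants would show a PDT-type change, and about 1 to 2 of 20 one that also aligns with T2, under linear recovery of 0.5 to 1.0 SD. A true 0.3 SD effect would give 20 × 0.10 = 2 of 20.

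These figures rest on the assumed recovery sizes and shapes, the protocol's autocorrelation of 0.30, 30% missing data, a two-sided 5% level and stand-ins for the PDT and the change-point method. The nine-day stagger and the PDT's disregard of the randomised start come from the protocol itself. The SCRT is not affected by this point.

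**What to change.** Replace the sentence in the Discussion with a statement of three things:
- Causal weight rests on the SCRT.
- Replicated PDT changes are reported as change over time during Booster.
- Replication and stage alignment do not rule out time since enrolment, because the stages differ by only about nine study days between participants.

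Report the planned ITSA trend result beside each PDT change as context. Do not make it a gate: with about 10% power at 0.3 SD it would discard nearly all the small effects of interest, and it is not robust to abrupt recovery near T2. A check of change dates against the assigned start day would add almost nothing, given the correlations of 0.01 to 0.15 in step 5.

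The cost is wording plus a reporting column from an analysis already planned. The downside is a weaker efficacy statement for small effects.
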